## Abstract

**Background:**

Few HIV antiretroviral adherence interventions target patients before they start treatment, assess adherence readiness to determine the timing of treatment initiation, or tailor the amount of adherence support. The Supporting Treatment Adherence Readiness through Training (START) intervention, based on the information-motivation-behavioral skills model of behavior change, is designed to address these gaps with the inclusion of (1) brief pill-taking practice trials for enhancing pretreatment adherence counseling and providing a behavioral criterion for determining adherence readiness and the timing of treatment initiation and (2) a performance-driven dose regulation mechanism to tailor the amount of counseling to the individual needs of the patient and conserve resources. The primary aim of this randomized controlled trial is to examine the effects of START on antiretroviral adherence and HIV virologic suppression.

**Methods/design:**

A sample of 240 patients will be randomized to receive START or usual care at one of two HIV clinics. Primary outcomes will be optimal dose-taking adherence (>85 % prescribed doses taken), as measured with electronic monitoring caps, and undetectable HIV viral load. Secondary outcomes will include dose-timing adherence (>85 % prescribed doses taken on time) and CD4 count. Primary endpoints will be month 6 (short-term effect) and month 24 (to test durability of effect), though electronic monitoring will be continuous and a fully battery of assessments will be administered every 6 months for 24 months.

**Discussion:**

If efficacious and cost-effective, START will provide clinicians with a model for assessing patient adherence readiness and helping patients to achieve and sustain readiness and optimal treatment benefits.

**Trial registration:**

ClinicalTrials.gov identifier NCT02329782. Registered on 22 December 2014.

**Electronic supplementary material:**

The online version of this article (doi:10.1186/s13063-016-1287-3) contains supplementary material, which is available to authorized users.

## Background

The success of HIV antiretroviral therapy (ART) remains dependent on high adherence [1–4]. While regimens have been simplified and are more forgiving, nonadherence is still a problem unsolved because many patients (40–70 %) have suboptimal adherence [5–7]. With the emergence of treatment as prevention [8] and patients starting ART earlier [9], often before having experienced any acute or advanced disease, the public health risks of nonadherence may be greater than ever. Studies suggest that patients with earlier-stage disease are less adherent to treatment [10, 11], and, if many patients are started on treatment before they are ready to adhere well, there is greater risk for an expanding community pool of resistance and less than adequate suppression of viral load and infectiousness to limit transmission. Treatment guidelines continue to emphasize the need for patients to be ready to adhere well before starting ART [9], but there are no established, reliable methods for determining pretreatment adherence readiness.

Most ART adherence interventions are designed to help patients achieve and maintain adherence readiness, but few target patients before they start treatment or tailor the amount of adherence support [12]. The Supporting Treatment Adherence Readiness through Training (START) intervention is based on the information-motivation-behavioral skills (IMB) model of behavior change [13]. It includes (1) brief pill-taking practice trials for enhancing pretreatment adherence counseling and providing a behavioral criterion for determining adherence readiness and the timing of treatment initiation and (2) a performance-driven dose regulation mechanism to tailor the amount of counseling to the individual needs of the patient and conserve resources. In a pilot randomized controlled trial [14], START had effects on both behavioral adherence and virologic suppression, unusual even for effective ART adherence interventions, which have typically improved one but not both of these outcomes [15]. The small sample size (*N* = 54) precluded adequate statistical power, but effect size estimates were 0.22 (dose-taking adherence), 0.75 (dose-timing adherence), and 0.41 (complete virologic suppression) over the first 6 months of treatment, with the latter two far exceeding the average 0.19 effect size found in a recent meta-analysis of ART adherence interventions that, like START, were not focused solely on patients already demonstrating adherence problems [12]. These promising results provide the rationale for the current, more rigorous, larger controlled trial of START.

In the present study, we are evaluating the effects of the START intervention on the primary outcomes of dose-taking adherence and undetectable viral load in a multisite randomized controlled trial, the protocol of which this article describes in detail. The primary objective of the study is to determine whether START is superior to usual care in helping patients achieve optimal (>85 %) dose-taking adherence, and complete viral suppression (undetectable HIV viral load) 6 months (short-term efficacy) and 24 months (long-term efficacy) after starting ART.

If effective, START will provide clinicians with an intervention that (1) informs providers and patients when the patient is ready to adhere well and start treatment, (2) enhances adherence readiness from the outset of treatment through the full course of therapy, and (3) tailors the amount of adherence support based on individual patient needs and performance, thus more efficiently using clinic resources, fostering better acceptance from providers and patients, and increasing the likelihood of successful program adoption and dissemination.

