## Methods/design

### Study design

In this multisite randomized controlled trial, we will evaluate the effects of the START intervention on ART adherence and HIV virologic suppression. We will recruit 240 patients with HIV at two HIV clinics, with each randomized to receive either START or usual care at a 1:1 ratio at each clinic (60 patients in each arm at each site). Random assignment codes will be computer-generated and placed in a sequential list that will be maintained by the principal investigator. Assignments will be issued to study coordinators once candidates have enrolled and completed the baseline survey. The randomization will be stratified by prior ART history (naïve or experienced) and CD4 count (<350 vs. ≥350 cells/mm^3^) because of the influence that prior ART history may have on adherence and clinical outcomes, and also due to our interest in determining whether early-stage patients can adhere as well as other patients to treatment. There is no way to blind the participants to whether they are receiving the intervention; this could potentially influence adherence performance and retention, as clients may feel more or less incentive to perform well in light of whether they receive the intervention. We do not see a way to prevent this potential bias, nor do we have a way to distinguish such effects from actual intervention effects; however, this limitation will be cited in reports of study findings.

Primary outcomes will be optimal dose-taking adherence (>85 % prescribed doses taken), as measured with electronic monitoring caps, and undetectable HIV viral load. Secondary outcomes will include dose-timing adherence (>85 % prescribed doses taken on time) and CD4 count. Primary endpoints will be month 6 (short-term effect) and month 24 (to test durability of effect), though electronic monitoring will be continuous and a fully battery of assessments will be administered every 6 months for 24 months. See Fig. 1 for the flow of participant procedures through the protocol. Participants will be paid $30 for each completed assessment, as well as a $50 bonus if they complete all five primary assessments and $10 for each attended intervention session. To limit attrition, contact information will be collected at enrollment and verified at each follow-up visit. Furthermore, the study coordinator will check with all study participants at the midway point between surveys, which will be timed to coincide with regular scheduled clinic appointments.

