### Study sample

Eligibility criteria include (1) patient and provider plan to start or restart (not currently on ART) the patient on ART; (2) patient has stable health status and no acute opportunistic infections or medical conditions (including acute HIV infection) that warrant starting ART immediately, as determined by the patient’s provider; (3) detectable HIV viral load at last test (within past 6 months); (4) if CD4 count is <200 cells/mm^3^, patient is on prophylactic medication to limit risks associated with the intervention’s imposed delay in starting ART; (5) patient is age 18 years or older; and (6) patient speaks English. Providers will inform eligible patients of the study, and patients who interested in participating will be referred to the study coordinator for consent procedures, eligibility screening, baseline survey, and randomization. Written informed consent will be obtained from all participants at enrollment. For control patients, the baseline visit is scheduled for the same day or within 1 week of the screening assessment. The baseline visit for intervention patients will take place on the same day as the last pretreatment intervention session (once they achieve >85 % dose-taking adherence during a practice trial).

We calculated the size of effects that this sample can detect with 80 % power (two-tailed test) with regard to the primary outcomes. On the basis of the pilot study [14], we expect that 40 % of the control group will achieve optimal (>85 %) dose-taking adherence and 45 % will achieve undetectable viral load. With these expected rates in the control group, together with estimates of 10 % and 30 % attrition at months 6 and 24, respectively, our sample size of 240 will be powered to detect a 9 % difference between the two arms with regard to both optimal dose-taking adherence and undetectable viral load at both months 6 and 24.

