***If dose-taking adherence to the practice trial is <85 %*****,** the patient will be given another 1-week supply of vitamins for the next practice trial and encouraged to use the strategies identified in the session to overcome adherence barriers during the coming week. Linking the doses to routinized daily activities will be discussed. For those who are unable to achieve 85 % adherence after completing four practice trials, the decision whether to start treatment will be left up to the patient and his or her provider. Adherence results from the practice trials are shared with the patient’s provider to assist in making this decision. Similarly, adherence data once the patient is on ART, but none of the survey data, will also be shared with the provider.

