#### ART adherence

Adherence to one of the vitamins in the practice trials for those in the intervention arm, and to one antiretroviral (with the most complex regimen) for all participants once ART is initiated, will be measured electronically and continuously throughout the study using the Medication Event Monitoring System (MEMS) caps. MEMS caps house a microelectronic chip that records the date and time of each bottle-opening, enabling a precise, objective assessment of the timing of each dose and the patient’s pattern of pill-taking. Participants will be instructed to refill the bottle when removing the last remaining dose, to use the bottle provided for the monitored medication, and to remove only one dose at a time when the medication will be ingested. Participants do not always follow these instructions (e.g., removing multiple doses at once or “pocketing,” or opening the bottle without removing a dose), so we will assess this via self-report using a “past 2 weeks” time frame at each primary assessment and will adjust the number of prescribed does taken during this time period, which has been validated and shown to strengthen the relationship between adherence and viral load [17]. We will ask patients to notify the coordinator if their provider changes their ART regimen.

Data taken from the caps are downloaded into a software file that calculates summary scores that include percentages of prescribed doses taken (dose-taking adherence) and prescribed doses taken within a specified window of time (dose-timing adherence). For the analysis, we will examine both mean dose-taking adherence and proportion with ≥85 % dose-taking adherence as primary outcomes, as well as mean dose-timing adherence and proportion ≥85 % dose-timing adherence as secondary outcomes. We will also ask participants to self-report the number of doses missed in the last week and percentage of prescribed medications taken in the last month, which will be used as secondary outcomes.

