### Data analysis

The primary aim of the analysis is to determine whether the START intervention is superior to usual care in helping patients achieve optimal adherence and virologic suppression in both the short and long term. Dose-taking adherence and viral load are the primary outcomes. Continuous adherence will be assessed for normality and transformed if needed; viral load data will be log-transformed. Our primary analysis is based on an intent-to-treat approach, with secondary analyses involving study completers. Attrition weights will be used to account for dropouts, and all analyses will incorporate design effects from this weighting in the calculation of standard errors and tests of significance. Analyses will be conducted to compare groups at months 6 and 24 to assess short- and long-term effects.

In addition to simple between-group comparisons at each time interval (baseline and months 6, 12, 18, and 24), we will conduct analysis of the trajectory of outcomes. Longitudinal analyses will be performed, using mixed effects models to examine differences in trajectories of adherence and HIV viral load across the two groups, controlling for patient characteristics. Linear mixed effects models will be used for continuous outcomes, while nonlinear mixed effects models will be used for binary outcomes (e.g., took at least 85 % of prescribed doses, undetectable viral load). Along with a fixed linear term for time, a random subject-specific intercept will be incorporated, with the appropriate covariance structure of the repeated measures being determined during analysis. Covariates added to the models will include components of our conceptual IMB framework and intervention (e.g., HIV knowledge, adherence motivation, adherence self-efficacy), as well as correlated process variables (e.g., number of practice trials completed, total number of sessions attended). To adequately model longitudinal HIV viral load, which has a high proportion of values below the limit of detection, a Bernoulli/log-normal random effects mixture model with left censoring will be used [18, 19]. Analysis of covariance will be used to define an effect size estimate in the analysis of the primary outcomes and to provide baseline adjustment to improve statistical power.

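### The primary endpoints run from ART start, a post-randomisation event that START itself influences, so randomised patients who never start have no defined endpoint in an analysis labelled intent-to-treat

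*Protocol article*

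**What the plan says.** - **Time origin.** The Background places the primary endpoints at "6 months (short-term efficacy) and 24 months (long-term efficacy) after starting ART". The Study design section repeats the time points with no origin: "Primary endpoints will be month 6 (short-term effect) and month 24 (to test durability of effect". Data analysis also gives none. The Background is thus the only place where the clock is defined.
- **Randomisation comes first.** Study design: "Assignments will be issued to study coordinators once candidates have enrolled and completed the baseline survey". No practice trial has taken place by then.
- **Only START alters ART start.** The Pretreatment training phase has up to four one-week practice trials before ART, and Study sample acknowledges that the intervention imposes a delay. For a START patient who does not reach 85% in four trials, "the decision whether to start treatment will be left up to the patient and his or her provider". Under Usual clinical care, practice trials are stated not to be part of the control condition.
- **Adherence exists only on ART.** Under ART adherence, the monitored antiretroviral "for all participants once ART is initiated, will be measured electronically and continuously throughout the study".
- **Viral load** comes from assays done routinely in clinic care and read from charts.
- **Analysis.** "Our primary analysis is based on an intent-to-treat approach", with attrition weights for dropouts and a completer analysis as secondary.
- **Baseline.** Study sample: "For control patients, the baseline visit is scheduled for the same day or within 1 week of the screening assessment", but "The baseline visit for intervention patients will take place on the same day as the last pretreatment intervention session", which is tied to passing a practice trial.

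**The concern.** Intent-to-treat compares everyone as randomised. Here the primary endpoint can be placed in time only for patients who reach an event after randomisation, and one arm is built to change when, and in some cases whether, that event occurs. START patients who fail all four trials and never start have been identified by poor pill-taking, the trait that the first primary outcome measures. If they are missing from the comparison, the START arm loses likely failures through a route that the control arm lacks.

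Two things are at stake. First, a difference in favour of START could partly reflect who is counted. Second, the weeks that START spends off ART are left out of the follow-up clock, so a comparison at equal time since randomisation, which would show any cost of the delay, is not specified.

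**Working it through.** **1. Order of events**

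| Step | Control | START |
|---|---|---|
| Baseline survey, then assignment (Study design) | yes | yes |
| Baseline visit (Study sample) | at screening or within 1 week | at the last pretreatment session, after passing a trial |
| Practice trials | none | up to four, one week each |
| After four failed trials | not applicable | ART start left open |
| Clock for months 6 and 24 (Background) | from ART start | from ART start |

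**2. What each kind of patient has**

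- *Prompt starter:* both outcomes, at defined times.
- *Delayed START patient:* both outcomes, measured later. The practice weeks are not counted.
- *Never-starter:* no adherence value and no month 6 or 24. Chart viral load may exist, but no date is assigned to it.

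The attrition weights are for dropouts. A never-starter who keeps attending is not a dropout, so the weights do not clearly apply.

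The baseline rows also conflict. In Study design the baseline survey precedes assignment; in Study sample the START baseline visit follows it. As worded, a START patient who never passes a trial has no baseline visit.

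**3. Possible size**

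The protocol gives no non-start rate in either arm, so there is no figure of its own to reproduce on this point.

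Inputs from the sample-size paragraph: control rates p = 40% (adherence) and 45% (undetectable); 120 per arm; attrition 10% and 30%, leaving 108 and 84 per arm.

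Assumptions: two-sided alpha 0.05 (not stated); no true effect; an excess share f of START never starts; all of them would have failed; they are left out.

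- START rate among starters: p_S = p/(1 − f)
- START number: n_S = n(1 − f)
- False gain: d = p_S − p
- Chance of a false favourable result: Φ[(d − 1.96·SE0)/SE1], with SE0 pooled and SE1 unpooled

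Example, adherence at month 6 with f = 10%: p_S = 0.40/0.90 = 0.444; n_S = 108 × 0.90 = 97.2; d = 0.0444; pooled rate 0.421; SE0 ≈ SE1 ≈ 0.0690. Then (0.0444 − 1.96 × 0.0690)/0.0690 ≈ −1.32, and Φ ≈ 9.4%.

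| Outcome | f | START rate | False gain (points) | False favourable, month 6 | Month 24 |
|---|---|---|---|---|---|
| Adherence, 40% | 5% | 42.1% | 2.1 | 5% | 5% |
| | 10% | 44.4% | 4.4 | 9% | 8% |
| | 20% | 50.0% | 10.0 | 29% | 23% |
| Viral load, 45% | 5% | 47.4% | 2.4 | 5% | 5% |
| | 10% | 50.0% | 5.0 | 11% | 9% |
| | 20% | 56.3% | 11.3 | 34% | 28% |

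The nominal value is 2.5%. The viral load rows are an upper bound, because chart results can exist for non-starters.

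As a yardstick, the excess that would by itself produce the protocol's 9-point difference in adherence is 1 − 0.40/0.49 = 18.4%. (That 9 points does not reproduce as the detectable difference: a standard two-proportion calculation at 108 per arm gives about 19. This is a separate matter and nothing here depends on it.)

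**4. Effect of keeping everyone**

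If non-starters are kept and counted as failures, the START rate is [p/(1 − f)] × (1 − f) = p, and this bias is zero.

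**The case against.** The strongest reply is that no sentence excludes non-starters. The analysis is called intent-to-treat, and a full statistical analysis plan is promised before unmasking, where outcome coding for such patients usually sits. That stands as far as it goes: exclusion is inferred. But the time origin is stated, not left open. A later plan can repair this only by departing from that clock or by adding an outcome rule for non-starters.

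Other parts of the reply also stand:

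- A reader might infer that delayed START patients drop out of the comparison. They do not; they are measured later.
- A reader might infer that attrition weighting passes the never-starters' weight to starters. The protocol does not say so; it ties the weights to dropouts.
- Failing four trials does not bar ART, and eligibility already requires a plan to start. Only patients who fail all four and then do not start are affected.
- Large excesses are hard to reach. Readiness on a once-daily regimen means 6 of 7 doses. With independent doses and no improvement between trials, a patient taking 80% of doses fails one trial with probability 0.423 and all four with 0.423⁴ ≈ 3%. At 70% of doses the figures are 0.671 and about 20%. Non-starters are a subset of these.
- Control patients may also never start. Only the difference between arms produces the bias.
- Scoring a patient with no prescription as not adherent is a choice of estimand, not a measurement.

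**Conclusion.** The concern holds in a limited form. The ART-start clock and on-ART adherence measurement leave randomised never-starters without a primary adherence outcome and without a defined month 6 or 24. They also leave START's practice weeks out of follow-up. Neither fits the intent-to-treat label, and the named attrition weights do not clearly close the gap. The problem is strongest for adherence; for viral load it is mainly an undefined date.

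The size is not known from the protocol. At a 5% excess of non-starters the false gain in adherence is about 2 points, with about a 5% chance of a false favourable result at month 6; at 10%, about 4 points and 9%; at 20%, about 10 points and 29%. These figures assume no true effect, that every excess non-starter would have failed, and that all are left out. A reader might take the upper end as the expected bias, or conclude that any START benefit would be an artefact. The protocol supports neither, since it gives no non-start rate and states no exclusion.

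**What to change.** Before unmasking:

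1. Define the primary analysis set as all 240 randomised patients.
2. Count a patient who has not started ART by the endpoint as not adherent and not suppressed. For this rule the endpoint date has to be counted from randomisation, since such a patient has no ART-start clock. Limit attrition weights to patients whose outcome is truly lost.
3. Add chart viral load at 6 and 24 months from randomisation beside the ART-start clock.
4. Report by arm the number never starting ART and the days from randomisation to ART start.
5. Keep the analysis of ART starters as secondary.
6. Reconcile the arm-dependent baseline visit in Study sample with Study design, where the baseline survey precedes assignment, and say which measurement is the baseline for analysis.

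The cost is analysis wording and a few extra tables; viral load is already drawn from charts. START patients will have up to about four fewer weeks on ART at the randomisation-based month 6, so the effect may look slightly smaller there. That difference is a real feature of the strategy.
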